### STEP interventions

#### Standard treatment for smoking cessation (ST)

All participants receive standard treatment for smoking cessation based on the most recent clinical practice guideline from the US Department of Health and Human Services, Treating Tobacco Use and Dependence [2]. This includes CBT for smoking cessation combined with NRT. This standard treatment is delivered through manualized once-weekly 60-min sessions over a 7-week period (Smoking Cessation Program; Therapist Guide [63]; see Figure 3). Topics discussed include identifying high-risk situations for smoking relapse, self-monitoring of cigarette consumption, identifying maladaptive thoughts and behaviors related to the maintenance of smoking patterns, enlisting social support, and developing coping strategies. The first 5 weeks of the intervention serve as planning and preparation weeks. The first day of week 6 of the study is designated as ‘quit day’, at which point participants are asked to make their quit attempt (see Figure 2). At this time, all participants will be given the option to start NRT. Participants are carefully educated about the proper use of the patch prior to quit day and are instructed to apply one patch daily. Based on the number of cigarettes they are smoking prior to quit day, clinicians offer patients a choice of 21-mg patches (indicated for those smoking >10 cigarettes per day), 14-mg patches (indicated for those smoking 10 or less cigarettes per day), or a 7-mg patch (indicated for those smoking <10 cigarettes per day). They gradually taper to a lower dose of the patch every 2 weeks. All participants are asked to taper off the lowest dose of the patch by week 14, at which time the patch is no longer provided. At each session while using the patch, participants are asked about current side effects they may be experiencing. Again, participants can also elect not to use the patch.

**Figure 3 F3:**
[figure not shown]
Overview of session objectives.

#### Exercise intervention (EX)

##### Intervention overview

One week following the baseline session, participants in the exercise condition initiate a 15-week program involving three 45-min exercise sessions each week. During weeks 1 to 7, the first weekly exercise session is completed following the CBT session. During the first session, clinicians provide participants with a rationale for exercise as a treatment for smoking cessation. They are given a model of the role of AS in the maintenance of smoking, and told how interoceptive exposure (exposure to aversive bodily sensations) plays a role in the treatment of AS. Exercise is then introduced as a means of systematic interoceptive exposure. Participants work together with their therapist to develop an exercise training progression schedule which allows participants to gradually increase their intensity across weeks to reach their prescribed dose by week 4 (see Figure 2). By week 4, participant’s target exercise intensity dose is 77% to 85% of their maximum heart rate (HR) achieved during the pretreatment maximal exercise test.

##### Exercise sessions

Trained and CPR-certified staff supervises exercise sessions. During the session, participants wear a HR monitor to confirm that they are training at the targeted exercise intensity. Participants commence the exercise session by performing an active warm-up of 5 min in duration at a progressively increasing speed until the corresponding dose is achieved. Participants then train at their target HR for 25 min. Five minutes after the warm-up (10 min into the exercise session) and every 5 min thereafter, participants are asked to rate their anxiety and/or distress level using the Subjective Units of Disturbance Scale (SUDS) [64]. Additionally, they are also asked their rate of perceived exertion (RPE) [65], speed, inclination of treadmill, and heart rate. At minute 25, participants initiate a 5-min cool down period during which their speed is gradually reduced. At 30 min, the exercise session concludes and participants stretch with the clinician. Occasionally, participants are reminded of and asked to explain the model and rationale for exercise reducing AS (either before or after the exercise session).

#### Wellness education intervention (CTRL)

Similar to the exercise intervention, the wellness education intervention is a 15-week program involving three 45-min sessions each week. The wellness education protocol was modeled after that used in previous studies of exercise for smoking cessation [60,66]. Specifically, during the first session, participants receive a thorough description of the wellness program along with a rationale for the intervention. Participants are given the rationale that, because people who quit smoking often adopt healthy lifestyle changes after smoking, we have opted to include these changes from the onset of the quit attempt to determine whether the addition of these lifestyle changes during a quit attempt has an effect on smoking cessation outcomes. They are also advised that focusing on small wellness goals each week and gaining small successes may carry over into their smoking cessation goals. Wellness education sessions focus on discussions of a variety of healthy lifestyle topics, such as healthy eating, stress and time management, recommended health screenings, and cancer and cardiovascular prevention. The content in each session is delivered using a combination of lectures, videos, handouts, and discussions while allowing participants to set their own realistic wellness goals, which they can gradually incorporate into their lives.

#### Assessment instruments

Table 1 provides an overview of the frequency and timing of administration for the primary assessments instruments that are used for screening, to measure post-cessation smoking outcomes and putative mediators, and to measure treatment integrity and acceptance. A description of each of these measures is provided next.

#### Measures for screening

##### Smoking history

Smoking history is assessed at Prescreen using indices agreed upon by a National Cancer Institute consensus panel [67]. These indices include measurements of brand and nicotine content of cigarette type, rate of smoking, previous quit attempts and duration, household smokers, age of onset of smoking, and more. This instrument has been successfully used in our previous work [43].

##### Anxiety sensitivity

The 16-item Anxiety Sensitivity Index (ASI-16; [25]) is employed to assess sensitivity to and discomfort with physical sensations. The ASI demonstrates good retest reliability and internal consistency, and excellent convergent validity with other established measures [68,69]. This measure is administered at Prescreen as an eligibility assessment.

##### Suicidality

The Columbia Suicide Severity Rating Scale (C-SSRS; [70]) is administered at Screening Visit 1. The C-SSRS is a standardized measure of current and past self-injurious behavior, suicidal intent, and suicidal behaviors, and demonstrates good reliability and validity [70,71].

##### Psychiatric diagnoses

At Screening Visit 1, the Structured Clinical Interview for DSM-IV non-patient version (SCID-NP) [72] is administered to determine diagnostic exclusions and lifetime prevalence of Axis I diagnoses. The SCID is administered by trained doctoral-level interviewers who are supervised by the senior investigators ([name] and [name]), as has been done successfully in the past (for example, [43,54]).

##### Medical history

The physician obtains medical history, which includes, but is not limited to, medical diagnosis, previous physical examination findings, history of symptoms, orthopedic problems, medication use, exercise history, and family history.

##### Physical exam

The physician completes a physical exam, which includes: height, body weight, apical pulse rate and rhythm, resting blood pressure, auscultation of the lungs, palpation of the cardiac apical impulse, point of maximal impulse, auscultation of the heart, palpation and auscultation of the carotid, abdominal, and femoral arteries, evaluation of the abdomen, palpation and inspection of lower extremities, tests of neurologic function, and inspection of the skin.

##### Laboratory testing

Laboratory testing is performed including hematology (for example, hemoglobin; hematocrit, red blood cell count (RBC); mean corpuscular hemoglobin (MCH), mean corpuscular hemoglobin concentration (MCHC); mean corpuscular volume (MCV), WBC with differential; and platelet count), biochemistry (sodium; potassium; calcium; chloride; glucose; triglycerides; cholesterol (total); protein (total); blood urea nitrogen (BUN); albumin; creatinine; alkaline phosphatase; bilirubin; aspartate aminotransferase (AST); alanine aminotransferase (ALT); and gammaglutamyl transpeptidase (γGT)), and serum pregnancy test (for women).

##### Maximal exercise testing

A maximal exercise test adapted from the Cornell protocol [73] is performed during screening (pretreatment) and at week 16 to examine the participants’ fitness level and obtain an assessment of maximum HR to formulate exercise dose. Though there are many protocols available for exercise testing, we chose the Cornell protocol because we feel it is less of a burden on participants, thus giving us more accurate results. The Cornell protocol is similar to the Bruce protocol; however, the Cornell protocol is divided into smaller and shorter stages and is generally more applicable to patients with limited exercise tolerance because of the smaller workload increments. Prior to the test, a resting ECG is taken and resting HR and blood pressure are measured. Participants then exercise at a rate that gradually increases in speed and incline in 2-min intervals for a maximum of 14 min. Participants are instructed that they may stop exercising at any point, but are encouraged to continue until they reach their maximal exercise dose. Maximal exercise is defined as an inability to continue exercise despite vigorous encouragement. Heart rate is measured continuously by ECG, and blood pressure is monitored every 2 to 3 min by recording brachial artery cuff pressure.

#### Measures of post-cessation smoking outcomes

##### Smoking status

Self-reports of smoking status are collected from participants weekly from quit day through Week 10 post-quit day and at Weeks 16 and 24 post-quit day. Participant reports of abstinence at all assessments are verified by expired carbon monoxide, and additionally with saliva cotinine at the 16- and 24-week interviews (see Table 1). The main outcome analyses are based upon 7-day point prevalence abstinence (that is, reported abstinence of at least 7 days prior to each scheduled follow-up). Self-report is always overridden by objective verification in the conservative direction [74].

In addition to point-prevalence outcomes, we also use the TLFB procedure for assessing the time to first smoking lapse and the time to first relapse, defined as the seventh day on which smoking occurs. The TLFB procedure demonstrates good reliability and validity [75] and we recently validated the TLFB for the assessment of adult cigarette use and to measure smoking among high AS persons over time [76]. The TLFB is administered at each assessment to assess cigarette use since the previous assessment.

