##### Biochemical verification

Self-reported abstinence at the 16- and 24-week follow-ups are verified by saliva cotinine (cutoff value of 10 ng/mL) for stated abstinence of 2 weeks or more (cotinine may be incompletely metabolized before this time), and carbon monoxide analysis of breath samples (8 ppm cut-off) for stated abstinence of 24 h to 2 weeks [62]. Saliva samples are frozen for shipment to an outside laboratory, which determines cotinine level by radioimmune assay. Expired air carbon monoxide levels are assessed with a carbon monoxide monitor [62]. Detected values above the stated cutoff scores are considered indicative of smoking.

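### Two sections give different biochemical verification rules for abstinence at weeks 16 and 24, and they disagree mainly for participants abstinent 7 to 13 days

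*Protocol article*

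**What the plan says.** The main outcome is 7-day point prevalence abstinence (PPA), defined under Smoking status as "reported abstinence of at least 7 days prior to each scheduled follow-up". The same section gives the first verification rule: expired CO for every report of abstinence, and "additionally with saliva cotinine at the 16- and 24-week interviews". It sets no condition on how long the participant has been abstinent. It adds that a test result always overrides self-report when the test points towards smoking.

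The next section, Biochemical verification, covers the same two visits and assigns a test by stated duration. Abstinence is "verified by saliva cotinine (cutoff value of 10 ng/mL) for stated abstinence of 2 weeks or more", and by "carbon monoxide analysis of breath samples (8 ppm cut-off) for stated abstinence of 24 h to 2 weeks". The reason given for the split is that "cotinine may be incompletely metabolized before this time". The section closes by saying that a reading above its cutoff counts as smoking.

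Table 1 marks both CO and cotinine in the last follow-up column without a condition, so both results may exist for the same person. Neither section refers to the other as governing, and neither says how a discordant pair of results is classified.

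**The concern.** At weeks 16 and 24 the two sections can give the same person different outcome values. The conflict matters most for abstinence of 7 to 13 days. The 7-day definition admits these participants. Biochemical verification sets cotinine aside for them because it may not have cleared, while Smoking status applies cotinine to them with an override that can only move them to smoking. Followed literally, the first rule can therefore fail someone whose report is true, by the article's own reasoning.

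The visits concerned carry weight. Power analyses states the primary hypothesis as PPA at the 6-month follow-up, which is week 24. Analytic methods instead focuses on the slope of PPA and treats single assessments as secondary. Weeks 16 and 24 are the last two points on that slope, so the conflict touches the data under either description.

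**Working it through.** The plan gives no figure on this point to reproduce. The check is a comparison of the two rules, followed by a bound on how many people could be affected.

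**Step 1: the rules side by side.** Both use the cutoffs given under Biochemical verification (CO 8 ppm, cotinine 10 ng/mL) and require at least 7 days' stated abstinence.

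- Rule A (Smoking status, weeks 16 and 24): abstinent if CO ≤ 8 and cotinine ≤ 10.
- Rule B (Biochemical verification, duration split taken alone): at 14 days or more, abstinent if cotinine ≤ 10; at 7 to 13 days, abstinent if CO ≤ 8.

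Illustrative values on each side of every boundary give eight patterns:

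| Stated days | CO (ppm) | Cotinine (ng/mL) | Rule A | Rule B |
|---|---|---|---|---|
| 10 | 3 | 4 | abstinent | abstinent |
| 10 | 3 | 25 | **smoking** | **abstinent** |
| 10 | 12 | 4 | smoking | smoking |
| 10 | 12 | 25 | smoking | smoking |
| 60 | 3 | 4 | abstinent | abstinent |
| 60 | 3 | 25 | smoking | smoking |
| 60 | 12 | 4 | **smoking** | **abstinent** |
| 60 | 12 | 25 | smoking | smoking |

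Two of the eight patterns differ, and Rule A is the stricter in both:

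- (a) 7 to 13 days, CO at or below 8 ppm, cotinine above 10 ng/mL;
- (b) 2 weeks or more, CO above 8 ppm, cotinine at or below 10 ng/mL.

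**Step 2: a ceiling for group (a).** Inputs from Power analyses: 150 participants, PPA 20% in ST+CTRL and 35% in ST+EX. Assumptions: 75 per arm, since the allocation ratio is not stated, and 5% to 15% of abstainers at week 24 abstinent for only 7 to 13 days, since the document gives no share.

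- Abstainers: 75 × 0.20 + 75 × 0.35 = 15 + 26.25 = 41.25, about 41.
- Abstinent 7 to 13 days: 0.05 × 41.25 = 2.1 to 0.15 × 41.25 = 6.2, about 2 to 6.

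Only those whose cotinine is still above 10 ng/mL change status, so 2 to 6 is the most that could change under the assumed share. Group (b) is not counted; nothing in the document allows an estimate.

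**Step 3: effect on the comparison, at that ceiling.** If the same share is lost from both arms, the 15-point difference becomes 15 × 0.95 = 14.25 points at 5% and 15 × 0.85 = 12.75 points at 15%. A loss in one arm only would move it more. At 10%, losing exercise abstainers gives 35 × 0.90 − 20 = 11.5 points, and losing control abstainers gives 35 − 20 × 0.90 = 17.0 points. The document gives no reason to expect a loss that differs by arm.

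**The case against.** The strongest reply is that the two sections are general and specific. Smoking status says which samples are taken and when. Biochemical verification follows directly, is the only place that gives cutoffs, and says how the results are used. Read together, CO applies throughout, cotinine is added at weeks 16 and 24, and it counts only at 2 weeks or more. This is a plausible reading, and the two sections can be reconciled, but the text does not state it. If the later section governs as written, CO does not verify claims of 2 weeks or more at these visits, and the statement that CO verifies reports at all assessments fails. If the earlier section governs, cotinine is used where the later one says it may mislead.

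For group (b) the reply is stronger. The closing sentence of Biochemical verification, taken with CO at every assessment and the one-directional override, makes it reasonable to count a CO above 8 ppm as smoking. High CO with low cotinine should also be rare, because smoking recent enough to raise CO would usually leave cotinine raised too. That softens (b). The sentence does not say which test applies to whom, however, and if it covered every sample taken it would also count cotinine at 7 to 13 days, against the section's own reason for the split.

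It can also be said that an article leaves the handling of discordant tests to a fuller document. That holds for omitted detail. Here the article states two rules that differ, so the point stands.

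**Conclusion.** The contradiction is real and concerns the definition of the outcome. Its main effect falls on group (a); group (b) is a lesser and probably rare conflict. The number affected is probably small and cannot be computed from the document. The figure of 2 to 6 participants is a ceiling that rests on an assumed 5% to 15% share and an assumed 75 per arm.

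A reader might infer several stronger points that the document does not support:

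- That the first rule turns the 7-day outcome into a 14-day one at weeks 16 and 24. It does so only for people who have not cleared cotinine, and the article says only that clearance may be incomplete.
- That the wording conflict is what makes verification tighten between weeks 10 and 16. Cotinine enters at week 16 under either rule, so some tightening follows from the schedule itself; the first rule adds to it by failing some true 7-to-13-day abstainers.
- That the rule will be picked once results are known. The full protocol or analysis plan may settle it, and neither is shown.
- That week 24 is undisputedly the primary analysis. Power analyses supports this, while Analytic methods puts the slope first.

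**What to change.** Before analysis, state one rule and use it in both sections. For example: CO at or below 8 ppm is required for every report of abstinence, and at weeks 16 and 24 cotinine at or below 10 ng/mL is additionally required only when stated abstinence is 2 weeks or more. Say how discordant CO and cotinine results are classified, and place a stated duration of exactly 2 weeks in one branch. Run the other reading as a sensitivity analysis.

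This stops cotinine from failing true 7-to-13-day abstainers. It does not make verification identical across visits, because a claim of 2 weeks or more still needs CO alone at week 10 and CO plus cotinine at weeks 16 and 24. That change should be acknowledged when the abstinence slope is interpreted, for example with a CO-only sensitivity analysis over all visits.

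The cost is wording and the extra sensitivity runs. Both samples are already planned, and the article reports the trial as still recruiting.

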##### Biochemical verification

Self-reported abstinence at the 16- and 24-week follow-ups are verified by saliva cotinine (cutoff value of 10 ng/mL) for stated abstinence of 2 weeks or more (cotinine may be incompletely metabolized before this time), and carbon monoxide analysis of breath samples (8 ppm cut-off) for stated abstinence of 24 h to 2 weeks [62]. Saliva samples are frozen for shipment to an outside laboratory, which determines cotinine level by radioimmune assay. Expired air carbon monoxide levels are assessed with a carbon monoxide monitor [62]. Detected values above the stated cutoff scores are considered indicative of smoking.

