##### Patient adherence

Patient adherence to the smoking cessation intervention, exercise intervention, and wellness program are assessed by taking attendance at each session (that is, number of total sessions attended). Adherence to the nicotine patch usage is assessed at Weeks 1 to 8 following the quit date. A significant difference in fitness (functional capacity) as expressed in METs between ST+EX and ST+CTRL conditions provides evidence of integrity of the exercise intervention. An assessment team that is blind to study condition will conduct the exercise testing.

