##### Concurrent treatment

Use of medications other than nicotine patch, other aids to smoking cessation, and participation in any concurrent psychotherapeutic treatment are assessed at each major outcome assessment (for example, baseline, quit date, weeks 2, 4, 8, 10, 16, and 24 following quit date) point.

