#### Inclusion of nicotine patch in standard treatment

Because recent clinical guidelines recommend that all smokers attempting to quit smoking receive pharmacotherapy [89,90], we believe it is important to make pharmacotherapy available as part of our standard smoking cessation treatment. We selected the transdermal nicotine patch (TNP) because of the extensive empirical literature supporting its effectiveness and safety, its ease of use, and its relatively benign side effect profile, which have led to its approval as an over-the-counter medication. We chose to provide the patch for 8 weeks because use of TNP for longer than 8 weeks does not appear to improve treatment efficacy [91]. Overall, using TNP with standard smoking counseling allows us to examine if the ST+EX is more efficacious than existing (standard) treatment. Because TNP is optional, its use will be tracked for each study participant.

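### The cotinine rule at weeks 16 and 24 has no exception for nicotine replacement, so a non-smoker using a nicotine product from outside the study is coded as smoking on the 6-month outcome

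*Protocol article*

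**What the plan says.** **The coding rule.** Under Smoking status, reported abstinence is "verified by expired carbon monoxide, and additionally with saliva cotinine at the 16- and 24-week interviews". Under Biochemical verification, abstinence at those two visits is "verified by saliva cotinine (cutoff value of 10 ng/mL) for stated abstinence of 2 weeks or more", while breath carbon monoxide (CO) serves shorter claims: "carbon monoxide analysis of breath samples (8 ppm cut-off) for stated abstinence of 24 h to 2 weeks". The consequence of a positive test is that "Detected values above the stated cutoff scores are considered indicative of smoking". Smoking status gives the order of precedence: "Self-report is always overridden by objective verification in the conservative direction". Neither section mentions nicotine replacement.

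**Patch supply.** The section on standard treatment offers the patch to everyone from quit day (study week 6) and stops providing it at study week 14. The rationale for including the patch cites its safety and ease of use, "which have led to its approval as an over-the-counter medication".

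**Records of nicotine-product use.** Under Patient adherence: "Adherence to the nicotine patch usage is assessed at Weeks 1 to 8 following the quit date". The Concurrent treatment section covers "Use of medications other than nicotine patch" together with further cessation aids and psychotherapy, at visits that include weeks 16 and 24. The patch rationale also says that patch use will be tracked for each participant, without giving an end date.

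**The concern.** Cotinine is a metabolite of nicotine, so a raised value shows exposure to nicotine, not to cigarettes. This trial teaches every participant about the patch, offers it to them, and notes that it can be bought without prescription. Its long-term verification test cannot tell a patch from a cigarette. Because the objective result always prevails, the rule as written leaves no room to correct a participant who is not smoking but still uses nicotine replacement.

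The people exposed to the error are those claiming at least two weeks of abstinence, who are the successes the trial hopes to count. The outcome affected is 7-day point prevalence abstinence (PPA) at week 24, which the Power analyses section names as the primary hypothesis. Miscoding at the same rate in both arms shrinks the difference. Miscoding at different rates biases it. Different rates are conceivable, since the Background says that exercise reduces withdrawal symptoms and continued nicotine use could follow withdrawal.

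**Working it through.** **Step 1: who can be miscoded.** Supply ends at study week 14. Quit week is study week 6, and 14 − 6 = week 8 after quitting, which agrees with the follow-up rationale. Cotinine is taken at weeks 16 and 24, so 16 − 8 = 8 weeks and 24 − 8 = 16 weeks after supply ends. Study patches used on schedule therefore cannot cause the error. Only nicotine replacement continued or obtained outside the study can.

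**Step 2: what is on record at those visits.**

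| Product at week 16 or 24 | Recorded? | Used by the coding rule? |
|---|---|---|
| Cessation aid other than the patch | Yes, under Concurrent treatment | No |
| Patch | Excepted from the medication item; dated assessment ends at week 8; undated promise of tracking elsewhere | No |
| Expired CO | Yes, under Smoking status and in Table 1 | Yes, but a cotinine result above the cutoff still counts as smoking |

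**Step 3: size, equal use in both arms.** The documents give no rate of outside use. Let *f* be the assumed share of true abstainers who are cotinine-positive from a nicotine product. Then recorded PPA = true PPA × (1 − *f*). True rates of 20% and 35% come from Power analyses. Taking 1:1 allocation of 150, the expected number miscoded is 75 × (0.20 + 0.35) × *f*.

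| *f* | ST+CTRL | ST+EX | Difference | Miscoded |
|---|---|---|---|---|
| 0 | 20.0% | 35.0% | 15.0 points | 0 |
| 5% | 19.0% | 33.3% | 14.3 points | about 2 |
| 10% | 18.0% | 31.5% | 13.5 points | about 4 |
| 20% | 16.0% | 28.0% | 12.0 points | about 8 |

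**Step 4: size, unequal use.**
- 20% in ST+CTRL, 10% in ST+EX: 0.20 × 0.8 = 16.0%; 0.35 × 0.9 = 31.5%; difference 15.5 points.
- 10% in ST+CTRL, 20% in ST+EX: 0.20 × 0.9 = 18.0%; 0.35 × 0.8 = 28.0%; difference 10.0 points.
- No true effect, both arms 20%: the first pattern records 16% vs 18%, the second 18% vs 16%. That is a spurious 2 points in either direction.

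**Step 5: power.** The plan states power above 0.80 for 20% vs 35% with 150 participants, from simulation. A single-time-point comparison of two proportions (75 per arm, two-sided 5%, both assumed) gives 0.54, so it does not reproduce that figure. The planned analysis is a repeated-measures GLMM, and the within-person correlation and trajectory behind the simulation are not given. The stated figure can be neither confirmed nor refuted here, and this point does not depend on it. On the simple test, power goes from 0.54 to 0.51, 0.48 and 0.43 for *f* = 5%, 10% and 20%. This shows the direction and rough proportion of the loss, not the power of the planned model.

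**The case against.** Several objections have force.

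- **Identification.** A reader might infer that users of nicotine replacement cannot be identified at all. The documents do not support that. Concurrent treatment covers further cessation aids at weeks 16 and 24, so users of non-patch products can be found. What stands is that the coding rule ignores this record.
- **Patch tracking.** A reader might also infer that patch use is definitely unrecorded after week 8. The patch rationale promises tracking with no end date. What stands is that the only dated assessment stops at week 8 and the later item excepts the patch, so no item clearly dated to weeks 16 and 24 captures it.
- **Reach of the rule.** Cotinine applies only to claims of two weeks or more, and supply ends 8 weeks before the first test. Both limit the group affected, which may be small. Neither removes the error for those in it.
- **Planned analysis.** The main model uses repeated assessments and focuses on slope, and cotinine enters only at the last two visits. The single-time-point power values therefore do not describe it. The week-24 classification is nonetheless wrong for the participants concerned.
- **Condensed article.** Form wording and exceptions may be left to a full protocol. That would answer a complaint of missing detail. Here, however, the article states a rule, says it always applies, and expressly excepts the one product the trial supplies. Followed as written, it misclassifies.
- **Conservatism.** Strict verification is a deliberate choice, and CO looks back over a shorter period. This is a real trade-off, and it is why cotinine-for-all should stay as a sensitivity analysis.

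**Conclusion.** The point stands in limited form. At weeks 16 and 24, a participant who has not smoked for two weeks or more but uses nicotine replacement from outside the study is coded as smoking, because the cotinine rule has no exception and always overrides self-report. The record of non-patch aids is not used to prevent this, and the passages on patch recording after week 8 need to be reconciled.

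The size is unknown. Under the assumed 5% to 20% of abstainers in both arms, the 15-point difference shrinks to between 14.3 and 12.0 points, or about 2 to 8 people in the trial. Unequal use can move the difference either way. A reader might infer a bias in favour of exercise, but the documents give no basis for a direction or for any particular rate of use. The conclusion also rests on two premises from general pharmacology, not from the article: cotinine rises with nicotine from any source, and nicotine replacement does not raise expired CO. The change is worth making because it is cheap and the rule decides the 6-month outcome, not because a large effect has been shown.

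**What to change.** 1. Include the patch in the concurrent-treatment item at weeks 16 and 24, so that all nicotine-product use is recorded there, and align this with the passages on patch adherence and tracking.
2. Add one sentence to Biochemical verification: participants who report any nicotine-product use at these visits are classified by expired CO at the stated 8 ppm cut-off in place of cotinine.
3. Report by arm how many participants are classified in this way.
4. Repeat the week-16 and week-24 results with cotinine applied to everyone who claims two weeks or more, as a sensitivity analysis.

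The cost is one added question on an existing form and one sentence in the rule; CO is already measured at both visits. The downside is that these participants are verified by a test with a shorter detection window, and that the switch depends on their own report of product use. Items 3 and 4 show how much the result depends on that.
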